### Sample size

The sample size was calculated with the online calculator “sealed envelope” (www.sealedenvelope.com). Two hundred thirty-two patients are required to have a 95% chance of detecting, with a significant level of 5%, a pain improvement difference of 10% between groups, considering a standard deviation of 10%, a success rate of the rehabilitation of 75% (i.e., for 4 patients included, one is expected to be randomized), and a dropout rate of 10%. The chosen pain improvement was expected to be of 50% into the control group and 60% into the experimental group. The standard deviation of 10% was estimated under the basis of a previous study of Mishra et al. [16]. Because the estimated standard deviation is not fully reliable and the calculated sample size is relatively small, the standard deviation will be re-evaluated and the sample size corrected accordingly if necessary to avoid a potential lack of power (*β*). It will be performed once the primary outcome is available for 40 patients.

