### Outcome measurements and assessments

The primary endpoint is the pain improvement between months 0 and 3 on a 0–10 visual analog scale (VAS) during a maximal strength isometric contraction of the extensor carpialis brevis muscle. Rationale: most specific clinical test in order to reproduce pain triggered by the tendon target of the intervention. Most clinical effects of the PRP use are awaited after 3 months of follow-up [18, 22]. The tendon healing will be evaluated with ultrasound in secondary outcomes. It was decided to use clinical parameters as primary outcome, because some pathological elements might persist on ultrasound after healing. Although the sensitivity of ultrasound is high, it does not reach 100% [23, 24].

Secondary endpoints:

Proportion of patients for which the tendon needling is not necessary after rehabilitation protocol

Clinical scores at − 3, 0, 3, 6, and 12 months of follow-up: (i) pain on a 0–10 (VAS) during a maximal strength isometric contraction at other timepoints; (ii) pain on a 0–10 VAS scale at rest; (iii) Single Assessment Numeric Evaluation (SANE) score; (iv) Patient-Rated Tennis Elbow Evaluation (PRTEE) score; and (v) maximal grip strength on Jamar test.

Ultrasonographic aspects of the epicondylar tendons at − 3, 0, 3, 6, and 12 months of follow-up: (i) volume of the lesion in mm^3^; (ii) Doppler reaction classified at the proportion of the tendon marked with the Doppler signal; (iii) solution of continuity in mm^3^; (iv) tendon thickness in mm; (v) concomitant superficial lesion and volume in mm^3^; and (vi) pain on a 0–10 VAS scale during sonopalpation.

It is worth noting that all post-intervention outcomes will be compared to their baseline values at month 0 in order to evaluate their net improvements.

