### Statistical analysis

The difference in primary outcome (pain improvement from baseline to 3 months post-intervention) between the treatment and control groups will be evaluated using the unpaired Student *T* test (or the Wilcoxon rank test when appropriate). The difference in secondary outcomes (changes from baseline to other time points) between the treatment and control groups will be evaluated with the appropriate statistical test (categorical variables: chi-squared, Fisher’s exact; continuous variables: Student’s or Wilcoxon rank tests). All analyses will be performed with an intention-to-treat analysis. Estimates of effect, 95% confidence intervals and descriptive *p* values will be reported whenever possible. In addition, graphs will be presented whenever possible.

Because the intervention is not considered at risk, not interim analysis is planned. However, in order to re-adjust the sample size calculation, it is planned to re-assess the standard deviation of the primary outcome for the 40 first allocated patients.

In case of missing data on the primary outcome, patients will be withdrawn. Patients with missing data for any of the secondary outcomes will be kept on the study, but excluded from the corresponding analysis.

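### The sample size is worked out for percent improvement, but the endpoint and test are described on a 0–10 VAS with no percent transformation, so the 95% power is not shown to apply to the planned test

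*Protocol article*

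**What the plan says.** The Sample size section states: "Two hundred thirty-two patients are required to have a 95% chance of detecting", "with a significant level of 5" per cent, "a pain improvement difference of 10% between groups, considering a standard deviation of 10" per cent. It adds: "The chosen pain improvement was expected to be of 50% into the control group and 60% into the experimental group". The SD is taken from a cited trial, and the protocol is frank about it: "Because the estimated standard deviation is not fully reliable and the calculated sample size is relatively small", the SD will be re-evaluated and the sample size corrected if necessary once the primary outcome is available for 40 patients.

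The section on outcome measurements says: "The primary endpoint is the pain improvement between months 0 and 3 on a 0–10 visual analog scale (VAS"), measured during a maximal isometric contraction. It closes by saying that post-intervention values are compared with month 0 to obtain net improvements. The Statistical analysis section tests "pain improvement from baseline to 3 months post-intervention" by an unpaired t test, or a Wilcoxon test where appropriate, and describes the secondary outcomes as changes from baseline.

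The endpoint and analysis text contains neither the word points nor any division by the baseline value. Nowhere is the 10% difference or the 10% SD converted to VAS units. The Discussion repeats the 10% difference without a unit.

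**The concern.** Percent improvement and improvement in points are different variables with different standardised effects. A patient's improvement in points is the baseline score times the fractional improvement, so its SD carries the spread of baseline pain between patients as well as the spread of response. A ratio of 1.0 on the percent scale becomes a smaller ratio on the point scale.

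The protocol gives some reason to expect baseline spread. The eligibility criteria set no minimum pain, patients are allocated if they are not satisfied after rehabilitation, and needling is withheld for success only when symptoms disappear. Partly improved patients can therefore enter alongside severely affected ones.

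At stake is the justification for randomising 58 patients. The same gap weakens the planned SD re-estimation: an SD observed in VAS points cannot be set against a target difference that exists only in percent.

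**Working it through.** **Inputs from the protocol.** Difference 10%, SD 10%, alpha 5% (sidedness not stated), power 95%, 1:1 allocation, dropout 10%, and "a success rate of the rehabilitation of 75% (i.e., for 4 patients included, one is expected to be randomized").

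**1. Reproducing the plan's figure.** Per arm, two-sided:

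n = 2 × (1.960 + 1.645)² × (10/10)² = 25.99, so 26; total 52.

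52 / 0.90 = 57.8, so 58 randomised; 58 × 4 = 232 enrolled.

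This matches exactly. A one-sided test would give 22 per arm and 49 randomised, so the calculation was two-sided. Power at 26 per arm is 95.0% by the normal approximation and 94.2% by the exact t test. The result uses only the ratio 10/10 = 1.0.

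**2. The same assumptions on the point scale.** Let P be the fractional improvement (mean p = 0.50 or 0.60, SD 0.10) and B the month-0 VAS (mean μ, SD σ), taken as independent. Improvement in points is P × B, so

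difference = 0.10 × μ

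variance in an arm = (0.01 + p²)(μ² + σ²) − p²μ²

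The two arm variances are averaged. The protocol gives neither μ nor σ, so **all values of μ and σ below are assumptions**.

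Example, μ = 7, σ = 1:
- control variance = 0.26 × 50 − 0.25 × 49 = 0.75
- experimental variance = 0.37 × 50 − 0.36 × 49 = 0.86
- pooled SD = √0.805 = 0.90; difference 0.70; ratio 0.78

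| Baseline mean, SD | Difference (points) | SD (points) | Ratio | Exact t-test power, 26 per arm |
|---|---|---|---|---|
| any mean, SD 0 | – | – | 1.00 | 94% |
| 8, 0.5 | 0.80 | 0.85 | 0.94 | 92% |
| 7, 1 | 0.70 | 0.90 | 0.78 | 79% |
| 7, 1.5 | 0.70 | 1.09 | 0.64 | 62% |
| 6, 2 | 0.60 | 1.27 | 0.47 | 39% |
| 5, 2.5 | 0.50 | 1.49 | 0.34 | 22% |

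Over means 5–8 and SDs 0.5–2.5 the range is 22% to 92%.

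**3. Adjusting for month-0 VAS under the same model.** With one common slope on baseline, the residual variance is about 0.01 × (μ² + σ²) + 0.05² × σ². At μ = 6, σ = 2 this is 0.40 + 0.01 = 0.41, residual SD 0.64, ratio 0.60/0.64 = 0.94, power 91%. Over the same grid, power is about 87% to 94%.

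**4. The other readings.**
- *Percent of baseline is analysed.* The ratio is 1.0 and the stated power stands. It depends on the 10% SD: at 15%, 20% or 30%, t-test power is 65%, 42% or 22%.
- *10% means 10% of the 0–10 scale.* The difference is 1.0 point with SD 1.0 point, and the stated power again stands. This implies mean improvements of 5 and 6 points. At an SD of 1.5 or 2 points, power is 65% or 42%.

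**The case against.** The best defence is that the protocol never says points. The outcome section names the instrument and not the derived variable, and the only section that puts numbers on pain improvement uses percent. On that reading nothing is miscalculated. This stands so far as it goes: a reader might infer that the protocol has a proven arithmetic error, or that the 95% is simply false, and the documents support neither. The figures reproduce exactly, and two readings leave the power intact. Still, simple change from month 0 is what the endpoint and analysis text most naturally describes, and the reading as 10% of the scale is strained.

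A second objection is that the power losses rest on assumed baselines and on independence of percent response from baseline. That is right. A reader might take power below half of the stated value as the finding, but it belongs only to the less favourable part of the grid. With a baseline SD of 0.5, power is still 87–92%.

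Third, the protocol doubts its own SD, plans to re-estimate it after 40 patients, and accepts that enrolment may have to exceed 232. That deserves credit and largely answers the worry that 10% is too small an SD. It does not answer the scale question, because recalculation needs a target difference in the unit of the re-estimated SD, and none is given on the VAS.

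Fourth, percent change is undefined at a baseline of zero and unstable near it. Since patients whose symptoms disappear are not needled, such baselines should be uncommon, so this is a minor argument.

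**Conclusion.** The point holds as a mismatch of scale. The 95% power is supported only for a variable whose difference-to-SD ratio is 1.0, and the protocol does not show that the variable it will test is such a variable. Under the ordinary reading, change in VAS points, power is overstated whenever baseline VAS varies. How much cannot be settled from the document: about 79% at baseline mean 7, SD 1; 62% at mean 7, SD 1.5; 39% at mean 6, SD 2, all resting on assumed baselines, the plan's own percentages, independence of response and baseline, and 26 evaluable patients per arm. If percent change is intended, the stated power stands on paper and the endpoint definition is what needs correcting. This is not a detail for a later analysis plan, because the unit underlies a figure that the protocol itself states and relies on.

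**What to change.** Name one analysed variable and use it in the endpoint, the test, the sample size and the re-estimation. The preferable choice is month-3 VAS in points adjusted for month-0 VAS, which is already collected; percent improvement can be reported descriptively. If the investigators prefer percent change, naming it explicitly as the primary variable would also remove the contradiction.

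Then:
- state the target difference and the residual SD in that unit;
- restate the power at 52 evaluable patients as a range over plausible SDs;
- specify that the re-estimation after 40 patients uses the same residual SD and the same target difference.

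Cost: one paragraph is rewritten and no new data are collected. The stated power becomes somewhat less favourable, about 87–94% with adjustment under the assumptions above, so slightly below 95%. A residual SD larger than assumed would still call for more patients, which the planned re-estimation could then properly detect.

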### Statistical analysis

The difference in primary outcome (pain improvement from baseline to 3 months post-intervention) between the treatment and control groups will be evaluated using the unpaired Student *T* test (or the Wilcoxon rank test when appropriate). The difference in secondary outcomes (changes from baseline to other time points) between the treatment and control groups will be evaluated with the appropriate statistical test (categorical variables: chi-squared, Fisher’s exact; continuous variables: Student’s or Wilcoxon rank tests). All analyses will be performed with an intention-to-treat analysis. Estimates of effect, 95% confidence intervals and descriptive *p* values will be reported whenever possible. In addition, graphs will be presented whenever possible.

Because the intervention is not considered at risk, not interim analysis is planned. However, in order to re-adjust the sample size calculation, it is planned to re-assess the standard deviation of the primary outcome for the 40 first allocated patients.

In case of missing data on the primary outcome, patients will be withdrawn. Patients with missing data for any of the secondary outcomes will be kept on the study, but excluded from the corresponding analysis.

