### Randomization and blinding

The allocation will be performed using computer-generated random number by serials of 4 patients blocks on a 1:1 ratio. Four strata will be used: (i) age 18–39 and absence of lesion on the superficial epicondylar tendon; (ii) age 18–39 and concomitant lesion on the superficial epicondylar tendon; (iii) age 40–65 and absence of lesion on the superficial epicondylar tendon; and (iv) age 40–65 and concomitant lesion on the superficial epicondylar tendon. The sponsor-investigator (AS) will generate 10 computerized allocation sequences. The secretary will randomly select one of those sequences for the study. The sponsor-investigator will enroll the participants and will perform the intervention 3 months after the recruitment. Patients will be allocated to a group at the time of the intervention, and only if the rehabilitation process was not successful. The unblinded co-investigator (MF) will access to the allocation on a sequentially numbered list and prepare the injection for the intervention in an opaque syringe (blinded content for AS). It is worth noting that this co-investigator will not take care of the patients subsequently.

This study is quadruple-blinded. Blinding concerns (i) the participants and (ii) the principal investigator (AS) during the intervention, (iii) the outcome assessment, and (iv) the statistical analysis. A complete masking of the intervention will allow the blinding of the participant and the principal investigator for the intervention and the outcome assessment. First, for all patients, the co-investigator (MF) will perform a blood puncture in room A. He will then go in room B and, depending of the allocation, prepare the PRP or turn-on the centrifuge for 5 min (sham PRP preparation). After that, he will prepare an opaque syringe containing either PRP or saline solution. In room A, the principal investigator will perform the ultrasound-guided fenestration of the ECRB tendon. During the fenestration, he will use the opaque syringe and inject the blinded content into the ECRB tendon. The statistical analysis (iv) will be performed by the principal investigator using a sham allocation list. Once the statistical analysis is completed, the true allocation list will replace the former list.

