The first main limitation is the small minimum sample size for the RCT (58 patients), chosen to detect a pain improvement difference of 10% between groups. Indeed, in case of success of the rehabilitation protocol, not more than 58 patients will be randomized. It could even be necessary to increase the initial sample size of 232 patients during the study. This small sample size of 58 patients might be prone to sampling variability, reason why stratification is planned. Authors consider that detecting a difference between groups smaller than 10% is not relevant, because the use of PRP should be supported by differences that are clinically relevant rather than statistically significant. PRP is considered as a safe treatment, widely used in sports medicine and promoted by medical companies. Financial interest might therefore easily influence the therapeutic decisions, even if the PRP cost-effectiveness has never been clearly demonstrated for tendon use [26–28]. The second main limitation concerns the inherent variability of the rehabilitation protocol. Indeed, like in virtually all case series with a rehabilitation protocol that include different items, the patient’s implication can differ. Moreover, it is difficult to apply the ESWT therapy with a strict standardized protocol for different reasons. First, because the benefits of ESWT treatment can be achieved after a variable amount of time, the rehabilitation length before the intervention varies between 3 and 6 months. Second, the tolerability and energy delivered can differ between patients. Finally, because the rehabilitation protocol including ESWT is applied to all patients, it is not possible to differentiate the effect of ESWT from other items of the rehabilitation.

The results of this study will provide insights into the effect of PRP as adjuvant therapy to tendon fenestration and may help identifying the best preceding and concomitant rehabilitation protocol.

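### The primary test is a valid but unadjusted comparison of change scores; adjusting for month-0 pain and the two stratification factors would use data already collected and usually gain precision

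*Protocol article*

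**What the plan says.** Under Outcome measurements and assessments, the protocol article defines the endpoint: "The primary endpoint is the pain improvement between months 0 and 3 on a 0–10 visual analog scale (VAS") during a maximal isometric contraction. The same section says that "all post-intervention outcomes will be compared to their baseline values at month 0 in order to evaluate their net improvements", so baseline is used by subtraction.

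Under Statistical analysis, the difference in that improvement "between the treatment and control groups will be evaluated using the unpaired Student" t-test, or a Wilcoxon test where that is suitable. Neither section names a covariate, a stratified test or a model.

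Under Randomization and blinding, allocation is by "computer-generated random number by serials of 4 patients blocks on a 1:1 ratio", and "Four strata will be used", formed by crossing age (18–39, 40–65) with absence or presence of a superficial tendon lesion. The Discussion gives the reason: "This small sample size of 58 patients might be prone to sampling variability, reason why stratification is planned".

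Under Sample size, the plan takes a difference of 10%, an SD of 10%, 95% power, a 5% significance level, 75% rehabilitation success and 10% dropout, giving 232 enrolled. It calls the SD not fully reliable and plans to re-estimate it, and the sample size with it, once 40 patients have the primary outcome.

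**The concern.** The trial stratifies because it is small and then analyses the data as if it had not stratified. Two separate losses can follow.

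- **Month-0 pain.** A change score fixes the slope on baseline at 1. If the correlation between month-0 and month-3 pain is below 1, with similar variances, change is itself correlated with baseline. A chance imbalance in month-0 pain then carries into the estimate. Regression on baseline estimates the slope and removes that component.
- **Strata.** If age group or lesion pattern predicts the outcome, balancing them by design reduces the true variance of the treatment difference. The t-test's standard error does not reflect this, so the interval is too wide and the test conservative.

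At stake is precision, and through the re-estimation the number of patients needed. By the plan's own assumption, each extra randomised patient costs about four enrolled.

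**Working it through.** **1. The plan's own figure.** The two-mean formula gives n per arm = 2 × (1.960 + 1.645)² × (SD/difference)². With SD 10 and difference 10 this is 25.99, so 26 per arm and 52 evaluable. Dropout: 52/0.9 = 57.8, so 58 randomised. Rehabilitation success: 58/0.25 = 232. This matches exactly, so sample size and test are consistent. Exact two-sided t-test power at 26 per arm and a standardised effect of 1.0 is 94%.

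**2. Month-0 pain.** Let ρ be the month-0/month-3 correlation and k the ratio of the month-3 SD to the month-0 SD. Neither is in the document; both are assumed over a range.

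- Change-score variance ∝ 1 + k² − 2ρk.
- ANCOVA residual variance ∝ k²(1 − ρ²).
- At k = 1 the ratio of the second to the first is (1 + ρ)/2.

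| ρ | k = 0.75 | k = 1 | k = 1.5 |
|---|---|---|---|
| 0.3 | 0.46 | 0.65 | 0.87 |
| 0.5 | 0.52 | 0.75 | 0.96 |
| 0.7 | 0.56 | 0.85 | 1.00 |

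At equal variances the variance is 35%, 25% or 15% lower, and the standard error 19%, 13% or 8% smaller. Over the whole grid the variance gain runs from about 0% to 54%.

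**3. Strata.** Suppose the strata explain a share R² of the change-score variance (assumed). With perfect balance, the actual type I error of the unadjusted test is 2 × [1 − Φ(1.96/√(1 − R²))]: 3.9% at R² = 0.1 and 2.8% at R² = 0.2. Incomplete blocks make balance imperfect. Simulations with 52 patients, four strata and blocks of 4 gave about 3.6–4.3% and 3.0–3.3%. In one set (ρ = 0.5), the mean reported standard error was about 0.277 SD against true values of about 0.268 and 0.249, an excess of about 3% and 11%. With non-prognostic strata, type I error was about 5%. ANCOVA with baseline and both factors held about 5% throughout.

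**4. If the SD is larger than planned.** Take a change-score SD of 15%, for illustration, with k = 1.

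- Power at 26 per arm, sample size unchanged: 65% unadjusted; 83%, 78% or 72% adjusted at ρ = 0.3, 0.5 or 0.7, allowing for three lost degrees of freedom.
- Sample size restored to 95% power, unadjusted: 25.99 × 2.25 = 58.5, so 59 per arm; 118/0.9 gives 132 randomised; 132/0.25 = 528 enrolled.
- The same, adjusted at ρ = 0.5: 58.5 × 0.75 = 43.9, so 44 per arm; 88/0.9 gives 98 randomised; 98/0.25 = 392 enrolled.

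The difference is 34 randomised and 136 enrolled patients, under these assumptions only.

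**The case against.** The case for leaving the plan alone is substantial, and most of it stands as a limit on the point.

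- **Validity.** A reader might infer that the test is invalid or biased, or that baseline is ignored. The document does not support this. Under randomisation the comparison of change is unbiased, its type I error does not exceed the nominal level, and baseline is subtracted.
- **Standard error.** A reader might infer that it is too large in any case. That holds only if age group or lesion pattern is prognostic, and the document gives no evidence either way. For month-0 pain the standard error is valid; the method is merely less efficient.
- **Power.** A reader might take 65% as the trial's power. That needs an SD of 15% and a sample size frozen at 26 per arm. The plan re-estimates the SD at 40 patients, and the Discussion accepts that enrolment may have to exceed 232. The realistic cost is more patients.
- **Size of the gain.** The 15–35% range rests on equal variances, which an expected improvement of 50–60% does not guarantee. The Sample size section also states effect and SD in per cent. If improvement means relative change, the formula in step 2 does not apply directly.
- **Choice between t-test and Wilcoxon.** The rule for switching is commonly left to an analysis plan, which is not shown, so it forms no part of this point.

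What survives is that the document fixes a specific primary test that omits its own stratification factors and makes weaker use of baseline than it could.

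**Conclusion.** The point holds as a recommended improvement in efficiency, not as an error that must be corrected for the trial to be sound. The analysis is valid and agrees with the sample-size calculation. It gives up precision: 15–35% of the variance at equal SDs and an assumed ρ of 0.7–0.3, with a wider range of roughly 0–54% if the month-3 SD is 1.5 to 0.75 times the month-0 SD. If the strata are prognostic it is also conservative: type I error of about 3.5–4.5% when they explain 10% of the variance, and about 3% when they explain 20%.

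On the planned SD of 10% the consequence is small, because power is already about 94%. It becomes material if the SD is larger, a possibility the protocol itself allows for. The magnitudes rest on ρ, k and R², none of which the document supplies.

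**What to change.** State one primary analysis: linear regression (ANCOVA) of month-3 VAS on treatment, month-0 VAS, age stratum and superficial-lesion stratum, reporting the adjusted difference with its 95% confidence interval. The endpoint need not change: with month-0 VAS in the model, month-3 VAS and absolute change give the same treatment estimate. Keep the t-test and Wilcoxon test as sensitivity analyses, use the same form of model for the continuous secondary outcomes, and base the 40-patient re-estimation on this model's residual SD.

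The cost is three degrees of freedom and no new data. Because the test stands in the protocol of a running trial, both the Statistical analysis text and the re-estimation text under Sample size would need amending, preferably before the 40-patient look.

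### The month-6 and month-12 secondary comparisons use available cases visit by visit and ignore earlier observed values; a repeated-measures model is a cheap improvement with a modest expected effect

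*Protocol article*

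**What the plan says.** All places are in the Methods of the protocol article.

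- **Visits** (Outcome measurements and assessments): "Clinical scores at − 3, 0, 3, 6, and 12 months of follow-up". In addition, "all post-intervention outcomes will be compared to their baseline values at month 0".
- **Comparison** (Statistical analysis): "The difference in secondary outcomes (changes from baseline to other time points) between the treatment and control groups" is tested by type of variable: "categorical variables: chi-squared, Fisher’s exact; continuous variables: Student’s or Wilcoxon rank tests". No repeated-measures model or imputation is named.
- **Missing secondary values** (Statistical analysis): "Patients with missing data for any of the secondary outcomes will be kept on the study, but excluded from the corresponding analysis".
- **Missing primary value** (Statistical analysis): "In case of missing data on the primary outcome, patients will be withdrawn".
- **Principle** (Statistical analysis): "All analyses will be performed with an intention-to-treat analysis".

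The article states both the tests and the exclusion rule, so this is a stated choice and not a detail left to an unseen analysis plan.

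**The concern.** A two-sample test on the change to one visit can use only the patients observed at that visit. The article does not say that each visit is tested separately, but the tests it names allow no other workable reading. Values at months 3 and 6 enter the tests for those visits; they do not inform month 12 for a patient who is absent then.

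Two things follow. First, the analysed set at months 6 and 12 is whoever attended, which is hard to square with an intention-to-treat claim for all analyses. Second, if attendance depends on earlier response, and does so differently in the two arms, the attenders are a differently selected group in each arm. At stake are the estimates and 95% confidence intervals that show whether a month-3 effect lasts. The month-3 primary comparison and the single-arm rehabilitation success rate are outside this point.

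**Working it through.** **1. The plan's own figure.** Inputs from Sample size: difference 10, SD 10, 5% significance (two-sided assumed), 95% power, 10% dropout, 75% rehabilitation success.

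- Per arm: 2 × (1.960 + 1.645)² × (10/10)² = 25.99, so 26 per arm and 52 in total.
- Dropout: 52 / 0.90 = 57.8, so 58 randomised, 29 per arm.
- Enrolment: 58 / 0.25 = 232.

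The stated 232 and 58 reproduce, and nothing below changes them. The planning effect is 10/10 = 1 SD.

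**2. Bias of the available-case difference at month 12.** The article gives 10% dropout and no other figure on loss, so the rest is assumed:

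- 29 per arm; normal changes at months 3, 6 and 12 with SD 1;
- a true difference of 1 SD, which is the month-3 planning effect carried to month 12;
- correlation between visits of 0.5 or 0.7;
- month-12 loss logistic in the month-6 value (slope 1.5), set to the stated percentage in each arm;
- 20,000 simulated trials per scenario.

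If the available numbers are n₁ and n₂, the standard error is about √(1/n₁ + 1/n₂):

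- 15% v 5%: √(1/24.65 + 1/27.55) = 0.277
- 20% v 10%: √(1/23.2 + 1/26.1) = 0.285
- 20% v 5%: √(1/23.2 + 1/27.55) = 0.282

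| Loss, saline v PRP | Bias, corr. 0.5 | Bias / SE | Bias, corr. 0.7 | Bias / SE |
|---|---|---|---|---|
| 15% v 5% | −0.055 | 0.20 | −0.076 | 0.27 |
| 20% v 10% | −0.052 | 0.18 | −0.073 | 0.26 |
| 20% v 5% | −0.079 | 0.28 | −0.110 | 0.39 |

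A likelihood estimate that uses the earlier visits is within 0.003 SD of the truth throughout. Coverage of the available-case 95% interval stays between 92.9% and 94.7%. At 15% v 5% the expected number missing is 29 × 0.15 = 4.35 v 29 × 0.05 = 1.45 patients.

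**3. When there is no bias.** With 10% response-dependent loss in each arm and the same mechanism, the bias is 0.003 SD or less at a true effect of 0 and of 1. The null rejection rate is 5.1%.

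**4. Precision.** With purely random loss in both arms, the ratio of standard errors (repeated measures to available case) is 0.983 at 10% loss and 0.973 at 15% for correlation 0.5. For correlation 0.7 it is 0.972 and 0.953. The gain is therefore about 2 to 5%, and it is established for random loss only.

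**5. A second mechanism as a check.** Means of 60 and 50 and SD 10 are carried to month 12. Loss depends on month-3 improvement, overall loss is 10%, correlation is 0.5 to 0.8, and there are 1,000,000 patients per arm. The true difference is 10.

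| Who tends to leave | Available-case difference | Loss, PRP v saline |
|---|---|---|
| Poor responders, same rule in both arms | 9.46 to 9.65 | 6% v 14% |
| Poor responders in saline only | 8.56 to 9.08 | 4% v 16% |
| Poor responders in PRP only | 10.59 to 10.97 | 10% v 10% |

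Using the month-3 value returns 10.0 to within simulation error in every row. The first row shows that one common rule yields unequal loss when the arms truly differ. The last row shows that bias can also favour PRP, and that equal percentages protect only if the mechanism is the same too.

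**The case against.** Comparing changes among available cases is an ordinary choice for secondary outcomes in a trial of about 58 randomised patients, and the article calls its p values descriptive. A bias of 0.2 to 0.4 standard errors hardly affects interval coverage. The loss rates, correlations and mechanism are all assumed, and the 1 SD effect belongs to the month-3 primary outcome. This stands, and it limits how strongly the change can be urged.

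Follow-up is also better protected than a bare reading of the analysis section suggests. Data collection and management says that missed appointments are rebooked by phone and that visits continue after protocol deviations. Table 1 records concomitant therapy and surgery through month 12. Patients and the outcome assessor are blinded. Study treatments and interventions mentions a possible second needling with PRP for those still symptomatic at the end, which is a reason to stay. These measures reduce missing values, but they do not change how the remaining ones are analysed.

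A reader might infer that the planned tests are valid only if values are missing completely at random. That is too strong: the comparison is also unbiased when loss depends on arm alone, and essentially so when response-dependent loss is the same in both arms (step 3). A reader might also infer that poor responders will leave, or that seeking other care makes their data missing. The article does not support the first, and its follow-up rules count against the second.

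Finally, the repeated-measures model is not a complete intention-to-treat analysis either, since patients with no post-intervention value still drop out of it. The rule that withdraws patients without the primary value is the plainer conflict with intention-to-treat, and a fix that left it standing would be incomplete.

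**Conclusion.** The point holds in a limited form. The plan fixes an available-case, visit-by-visit comparison that does not use earlier post-intervention values and fits poorly with its intention-to-treat statement. Bias at months 6 and 12 is possible, not shown. It needs loss that depends on earlier response and differs between arms in amount or mechanism. Under the assumed losses of 15% v 5% to 20% v 5% it is about 0.05 to 0.11 SD, which is 5 to 11% of the planning effect. In those scenarios it understates a benefit of PRP; under other mechanisms it could overstate one. With equal loss from the same mechanism, bias is essentially nil, and under random loss the benefit of the model is a 2 to 5% smaller standard error. No confirmatory conclusion rests on these comparisons, so the change lies between optional and recommended.

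**What to change.** 1. **Approximately continuous secondary outcomes (VAS, SANE, PRTEE, grip strength).** Fit one mixed model for repeated measures to the change from month 0 at the scheduled post-intervention visits. Include arm, visit, arm-by-visit, the month-0 value and the randomisation strata, with unstructured covariance. Include every randomised patient with at least one post-intervention value. Report the arm difference with its 95% confidence interval at each visit.
2. **Planned visit-by-visit tests.** Keep them as a sensitivity analysis and reword the exclusion sentence to match.
3. **Ultrasound and categorical outcomes.** Lesion volumes and the Doppler proportion may be skewed or zero after healing, so transform them or keep rank tests. Keep the planned tests for categorical outcomes.
4. **Patients without the month-3 primary value.** State that they stay in follow-up and in these models. Otherwise the withdrawal rule would remove their month-6 and month-12 data.
5. **Intention-to-treat wording.** Say which patients each analysis includes, so that the claim and the analysed sets agree.

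The cost is wording and a little more programming in R, which the trial already uses to compile its visits. No extra patients, visits or staff are needed. The downside is that the model relies on values being missing at random given the observed data, which the trial cannot verify.
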